## Abstract

**Background:**

In recent years, the number of arthroscopic shoulder surgeries has increased given that the intervention is minimally invasive. However, postoperative pain is one of the most common symptoms of patients who undergo arthroscopic surgery. Although pharmacological treatments and brachial plexus blocks for reducing pain are currently used, the adherence rate of interventions is low, and adverse effects often occur. Chimsband, made up of silver and optic fibres, is a novel taping therapy that stimulates patients’ acupoints and is expected to relieve pain with few adverse effects. The aim of this study is to explore the effectiveness of Chimsband to relieve pain following arthroscopic shoulder surgery.

**Methods/design:**

This is a randomised, parallel, controlled, exploratory clinical trial. Thirty participants who undergo arthroscopic shoulder surgery will be randomly allocated to an intervention or a control group. Both groups will receive 10 sessions of interferential current therapy within a period of 2 weeks, while the intervention group will additionally receive taping therapy after undergoing physical therapy. Two follow-up visits will be scheduled after the last treatment session. The primary outcome variable will be the difference in the visual analogue scale (VAS) scores between baseline and first follow-up evaluation after the end of 10 treatment sessions. The secondary outcomes will be VAS at the end of the second week, shoulder pain and disability index, range of motion, VAS while sleeping, questionnaire of blood stasis pattern identification at two follow-up visits, and number of bands used per visit. Outcomes will be evaluated at baseline, 2 weeks from visit 1 (+ within 6 days) after commencement, and at 4 weeks from visit 1 (+ within 6 days) follow-up.

**Discussion:**

This study will be the first clinical trial to explore the effect and safety of Chimsband on postoperative shoulder pain. It would provide clinical evidence to conduct further taping therapy studies for relieving musculoskeletal pain.

**Trial registration:**

Korean Clinical Trial Registry, KCT0002355. Registered on 13 June 2017.

**Electronic supplementary material:**

The online version of this article (10.1186/s13063-018-2866-2) contains supplementary material, which is available to authorized users.

## Background

Shoulder arthroscopy is a minimally invasive surgical technique to treat shoulder pathology in the shoulder area [1]. Recently, there has been a preference by patients with shoulder injuries for arthroscopic surgery because of the short inpatient period and fast postoperative recovery [2]. The number of arthroscopic shoulder surgeries has increased by 600% from 1996 to 2006, while that of open rotator cuff repairs has increased only by 34% in the United States [3]. In Korea, over a period of 5 years (from 2010 to 2014), the number of patients with shoulder disease increased by an average of 4.6%, and medical expenses increased by an average of 13.3% annually. The number of shoulder surgeries (acromioplasty and ruptured rotator cuff repairs) reached 56,000 cases by 2014 [4] (http://www.medipana.com/news/news_viewer.asp?NewsNum=165805&MainKind=A, http://www.akomnews.com/?p=330302).

Patients who underwent arthroscopic shoulder joint surgery tended to experience more postoperative pain with delayed rehabilitation and increased dissatisfaction with surgical results compared to patients who underwent other arthroscopic surgeries [5, 6]. Pharmaceutical treatments are currently used to relieve postoperative pain. However, NSAIDs and long-term narcotic analgesics can induce nausea, vomiting and risk of addiction. A persistent brachial plexus block technique can be utilised in limited cases, as the risk of infection can increase. New treatment technologies such as non-pharmacological therapies and rehabilitation treatments with strengthening muscles that have fewer adverse effects (AEs) and are more effective are required [7].

There are several reports of complementary medicine that directly stimulate acupoints such as ST36, LI4 and ST6 as well as proximal points of painfulness area to control postoperative pain [8, 9]. Patients who underwent neck dissection and received acupuncture had increased Constant–Murley scores when evaluating pain and had improved shoulder function [10]. Electroacupuncture treatment also reduces postoperative thoracic pain [11]. Studies regarding indirect stimulation of acupoints, such as the PC6 (pericardium-6: Neiguan) point stimulation band, made up of a wrist band and a bead to stimulate the acupoint, which is effective for postoperative nausea, have been published as study protocols [12], while the effectiveness of indirect acupoint-stimulating therapies to relieve postoperative pain is still unknown.

Chimsband (Chimsband; Chims-Saengvit Oriental Medicine Clinic, Seoul, Korea) is a taping therapy invented by a Korean medical doctor, and it is also the name of a medical device. Chimsband comprises thin silver layers and optic fibres with an adhesive patch, with high electric and photic conductivity (Fig. 1). Painful areas have deviant bioelectric currents, and the fibres in Chimsband are supposed to recover abnormal areas on a patient’s body by equalising the biocurrent between normal area and painful sites. Although there are some case studies of Chimsband application for headache, paresthesia, chronic pain, diarrhoea, rhinitis, and depression, no randomised clinical trials to evaluate its clinical effectiveness have been conducted [13, 14].

**Fig. 1 Fig1:**
[figure not shown]
Appearance of Chimsband. **a** Individual Chimsband. **b** One set of Chimsband

This study is being conducted in order to explore the effectiveness and safety of Chimsband to control postoperative pain. The participants will be patients who have undergone arthroscopic shoulder surgery who have postoperative pain. This study will generate basic evidence on the effect of Chimsband and direct the topics of further studies. We hypothesise that treatment with Chimsband in addition to interferential current therapy (ICT) will be more effective than ICT treatment alone. We will test this hypothesis by a randomised controlled pilot trial. This study protocol was written in accordance with the Standard Protocol Items: Recommendations for Interventional Trials (SPIRIT). The SPIRIT checklist has been included in Additional file 1.

## Methods

### Design

This is a randomised, controlled, parallel-designed, exploratory clinical trial. It is an open-label study that will be conducted at DongShin University Gwangju Oriental Hospital, Korea.

Thirty participants who voluntarily submit written informed consent will be randomly allocated to either the intervention group or the control group if the participant is deemed eligible to enter the clinical trial. Both groups of participants will receive ICT therapy because of ethical issues. The intervention group participants will additionally receive 10 sessions of Chimsband therapy over a period of 2 weeks (+ 6-day window), while the control group participants will not receive band therapy. After intervention, both groups will be evaluated at week 4 from visit 1 (+ 6-day window), and the clinical trial will end after the follow-up assessment on each variable at week 4 from visit 1(Fig. 2).

**Fig. 2 Fig2:**
[figure not shown]
Flowchart of the clinical trial

### Inclusion criteria

Patients with postoperative pain after arthroscopic shoulder surgery who meet the following criteria will be included:Between 19 and 69 years old (either sex)Pain in the shoulder area after arthroscopic shoulder surgeryUnderwent surgery within the past 2 years and at least 2 weeks previously (whose surgical fixation area has completely healed)Visual analogue scale (VAS) score for pain is greater than 40 on initial screeningVoluntarily participated in the trial and submitted a written informed consent form

### Exclusion criteria

Patients meeting any of the following criteria will be excluded:Patients who do not submit documentation that can verify arthroscopic shoulder surgery history (surgery admission letters, medical opinions, diagnosis form or medical certificates)Patients who have contact dermatitis or scars surrounding the surgical sites and whose clinicians diagnosed them as inappropriate to enter the trialPatients who have used narcotic analgesics upon initial screeningPatients with a clinical diagnosis of acute inflammation, including suppurations surrounding the shoulder surgery area and swelling or any laboratory test result that is more than 1.5 times that of the upper or lower limit of normal range during the screeningEnrolled in other clinical studiesParticipants with drug or alcohol abuse history or suspicious of thoseAccommodated in residential institutions such as social welfare institutions

### Randomisation and allocation concealment

A statistician not involved in the conduction and evaluation of the clinical trial will make the allocation list by block randomisation using Statistical Analysis System (SAS)^®^ Version 9.4 (SAS institute. Inc., Cary, NC, USA). The participants will be randomly assigned in a 1:1 ratio to the intervention group or control group. Participants who signed a written consent form will receive individual screening numbers. If the potential subject is eligible to participate in the clinical trial by screening, the statistician will allocate the randomisation numbers sequentially and finally determine the subject identification code. Once the number is allocated, reuse of the number is prohibited. If screened participants are not randomly allocated, the clinical research coordinator will record the individual numbers of participants not allocated and the reason patients were not allocated on the case report form.

Random allocation codes will be stored in opaque envelopes and kept in a double-locked cabinet. If the investigator decides to enrol a subject who signs informed consent and meets the inclusion/exclusion criteria, the investigator will open the randomised allocation envelopes in sequence with the participants and allocate subjects to each group. The investigator will record the opening date, sign the opened envelopes and store them separately.

### Interventions

The intervention group will receive ICT and additionally receive Chimsband therapy for 10 sessions over a period of 2 weeks. The control group will only receive ICT therapy. All intervention practitioners will not be involved in outcome assessment procedures.

#### Interferential current therapy (ICT)

The physical therapist will carry out ICT to all participants one time per visit (visit 1 to 10), taking into consideration patients’ shoulder and pain status. The ICT instrument will be the IN-2200 from the Youngin-Medical Corporation, the transportation frequency will be 3750 to 4000 Hz, and the interferential frequency will be 0 to 250 Hz, set to the automatically changed mode. A four-pad electrode will be arranged in a crisscross pattern on the patients’ area of pain. The current strength for therapy will be set at the level of patient tolerance. Strength will be printed in interrupt mode, and adaption time will be 20 min. For the treatment group, the physician will perform physical therapy after removing the Chimsband, and new Chimsband will be attached to the patient’s shoulder when the physical therapy ends.

#### Intervention group

There will be 10 treatment sessions over a period of 2 weeks (+ 6-window days), and physicians will attach Chimsband to patients at each visit. For the treatment group, Chimsband will be attached on the painful shoulder area, where acupoints LI15, LI16, GB21, SI10, and TE14, and Ashi points are located (Fig. 3). Physicians will define the Ashi points that produce a painful or uncomfortable sensation with pressure [15]. Only painful points located in the shoulder-dorsal area, cervicothoracic area and upper limb muscle area will be accepted. Patients will visit the physician at 2 and 4 weeks after visit 1 (+ 6-window days) to assess the effectiveness and safety of the treatment.

**Fig. 3 Fig3:**
[figure not shown]
Intervention of Chimsband

#### Control group

This trial proposes evaluating the overall effectiveness of Chimsband for postoperative pain. To reflect real-world treatment, the control group will be assigned to receive physical therapy. Physical therapists will carry out only ICT to the control group participants one time per visit. The treatment session will be 10 times over a period of 2 weeks (+ 6-window days). Patients will visit the physician at 2 and 4 weeks after visit 1 (+ 6-window days) to assess the effectiveness and safety of the treatment.

### Concomitant treatments

All participants in the intervention and control groups will be asked not to take other therapies intended to reduce postoperative pain from arthroscopic shoulder surgery other than the treatments in this clinical trial. If the participants have undergone continuous treatment before enrolling in the trial, there should be no changes in this treatment during the study period. All patients should report new treatments to the clinical trial institution when therapies are started after entering the clinical trial.

### Primary clinical outcomes

The primary outcome is shoulder pain and will be measured by the VAS measured at visit 11. If the score exceeds 40 points on screening, the participant will be enrolled in the study. Visit 11 will be at visit 1 + 2 weeks + 6-window days (last Chimsband attachment or ICT + 6-window days), as first follow-up date [16].

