### Secondary clinical outcomes

The secondary outcomes will be pain VAS at visit 12, Shoulder Pain and Disability Index (SPADI), range of motion (ROM), shoulder pain VAS while sleeping, blood stasis pattern identification questionnaire, and number of bands used per patients on each visit. All questionnaires will be presented in Korean.

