#### General rule of data analysis

All statistical analyses in the trial will be two-sided sets, and *p* values will be 5%. SAS^®^ Version 9.4 will be used to analyse the data.

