#### Primary clinical outcomes

Mean VAS variation difference between visit 1 and 11 will be tested by the following hypothesis.

Null-hypothesis (H0): There is no difference in the mean VAS variation between before and after treatment in each group.

Alternative hypothesis (H1): There is a difference between the mean VAS variation before and after treatment in each group.

Mixed-effect Model Repeated Measures (MMRM) will be adapted for fixed factors, namely treatment groups and visiting time, while random factors will be the participants in the trial.

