#### Secondary clinical outcomes

VAS at visit 11, SPADI, ROM, VAS while sleeping, questionnaire of blood-stasis pattern identification, and the number of used bands on visits 11 and 12 (secondary follow-up, fourth week from visit 1 with + 6-day window) will be analysed by the same method as in the primary effectiveness evaluation. For analysing the difference of measurement value between before and after treatment in each group, Student paired *t* test or Wilcoxon signed-rank test will be adapted for effectiveness evaluation variables. To test the difference related to variations of VAS per visit, repeated measures analysis of variance will be conducted, and the adjustment method of multi-comparison will be Dunnett’s procedure. In addition, the subgroups will be analysed depending on the pain severity or post-operation stage.

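### The primary outcome is the visit-11 VAS level in one section and the change from visit 1 to visit 11 in two others, and the week-2 VAS is also listed as secondary

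*Protocol article*

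**What the plan says.** The protocol article describes the primary outcome in three places.

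- Methods, Primary clinical outcomes: "The primary outcome is shoulder pain and will be measured by the VAS measured at visit 11". No baseline and no change is mentioned. The rest of the paragraph gives the entry threshold and the timing of visit 11 (two weeks after visit 1, plus a six-day window).
- Abstract, Methods/design: "The primary outcome variable will be the difference in the visual analogue scale (VAS) scores between baseline and first follow-up evaluation".
- Statistical analysis, Primary clinical outcomes: "Mean VAS variation difference between visit 1 and 11 will be tested by the following hypothesis". The model is an MMRM that "will be adapted for fixed factors, namely treatment groups and visiting time, while random factors will be the participants in the trial". Baseline VAS is not named as a covariate.

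The VAS also appears among the secondary outcomes, at two different time points.

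- Abstract: "The secondary outcomes will be VAS at the end of the second week".
- Statistical analysis, Secondary clinical outcomes: the list opens "VAS at visit 11, SPADI, ROM, VAS while sleeping".
- Methods, Secondary clinical outcomes: "The secondary outcomes will be pain VAS at visit 12".

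Week 2 is visit 11 and week 4 is visit 12, so the first two entries name the primary time point and the third names the later one.

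**The concern.** The section whose job is to define the primary outcome gives a final value, while the abstract and the analysis section give a change score. The visit-11 VAS is therefore primary in one place and secondary in two others. A reader has to decide which statements are slips before knowing what is primary.

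The choice affects the result. Unless baseline is adjusted for, level and change give different estimates, standard errors and p values. The trial is open-label, plans 12 evaluable participants per arm, and tests at a two-sided 5% level. In that setting one fixed definition is the simplest protection against settling the metric after the data are seen.

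**Working it through.** **The plan's own figure.** The article takes 12 per group from a pilot-study recommendation and allows 20% dropout: 12 / (1 − 0.20) = 15 per group, 30 in total. This reproduces. It uses no effect size, SD or power, so it does not depend on whether the outcome is a level or a change.

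**The definitions side by side.**

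| Place | Primary VAS | Secondary VAS |
|---|---|---|
| Abstract | change, baseline to first follow-up | week 2 (visit 11) |
| Methods, outcome sections | level at visit 11 | visit 12 |
| Statistical analysis | change, visit 1 to visit 11 | visit 11 |

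Scale and visit agree throughout the primary column; the metric does not. The secondary column disagrees on the visit.

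**How far apart level and change can be.** Let B be the visit-1 VAS and F the visit-11 VAS, with complete data and no adjustment.

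- Level estimate: mean F (intervention) − mean F (control).
- Change estimate: mean (F − B) (intervention) − mean (F − B) (control).
- Level minus change: mean B (intervention) − mean B (control), the chance baseline difference.

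Under randomisation this gap has mean zero and standard deviation s × √(2/n), where s is the baseline SD and n the number per arm. The article gives no SD, so s = 12 to 20 is an assumption. As a plausibility check, values spread evenly from 40 (the entry threshold) to 100 would have an SD of 60/√12 = 17.3.

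- n = 12, s = 12: 12 × √(2/12) = 4.9 points
- n = 12, s = 20: 20 × √(2/12) = 8.2 points
- n = 15, s = 20: 20 × √(2/15) = 7.3 points

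**Precision differs too.** If both visits have SD 20 (assumed), the standard error of the level estimate at 12 per arm is 8.2. The SD of a change is 20 × √(2(1 − ρ)), where ρ is the baseline to visit-11 correlation. That gives 23.7, 20.0 and 15.5 at ρ = 0.3, 0.5 and 0.7. Multiplied by √(2/12), the standard errors are 9.7, 8.2 and 6.3. Change is less precise than level when ρ is below 0.5 and more precise above it.

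**What baseline adjustment does.** Write F = a + t·G + b·B + error, where G is the group. Subtracting B from both sides gives F − B = a + t·G + (b − 1)·B + error. The treatment effect t and its standard error are unchanged. A check fit to one simulated data set of 24 gave −5.90 with p = 0.497 for both outcomes.

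**Illustration only.** In 20,000 simulated trials per setting (SD 20 at both visits, ρ = 0.3 to 0.7, 12 per arm, unadjusted two-sample t tests), a true difference of 20 points gave different verdicts at p < 0.05 in 32% to 33% of trials. With no true effect, at least one of the two tests was significant in about 9%.

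**The case against.** The best defence is that the Methods paragraph names the domain, the instrument and the time point, and leaves the metric to the analysis section. The two places that do state a metric agree on change, and the only primary hypothesis written down is on change. Anyone reporting the visit-11 level as primary would contradict the abstract and both analysis paragraphs. Much of this stands. A reader might infer that the trial has two primary endpoints, either of which could be reported as pre-specified. The document does not support that: no passage specifies a primary test of the level.

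The defence does not clear up the whole text, however. If the visit-11 level is meant as a secondary outcome beside a primary change, the Methods section should not call it primary, and the Methods list of secondary outcomes should not name visit 12 instead. If the secondary entries are slips for visit 12, two places need correcting. Either way the text must be reconciled.

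A second objection concerns the simulated figures. They rest on assumed SDs, correlations and effect, ignore the entry threshold, and use unadjusted t tests rather than the stated MMRM. The 9% also requires someone to choose the metric after seeing both results. Further, a covariate the article does not list is not thereby excluded, since the full plan may name it, and with baseline in the model the disagreement vanishes. This stands. It is why a claim that about a third of such trials would give conflicting verdicts should not be read as a property of this trial, and why the missing covariate is not itself the fault.

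**Conclusion.** Wrong as written, low to moderate severity. The metric of the primary outcome conflicts between sections, and the same measurement appears as both primary and secondary. It is one endpoint with conflicting definitions, and the weight of the text favours change.

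The size that can be defended is the gap between the two unadjusted estimates: a standard deviation of about 5 to 8 VAS points at 12 per arm. It assumes complete data and a baseline SD of 12 to 20. With baseline accounted for, the gap in the treatment effect is zero. The trial is exploratory and its sample size is unaffected, which keeps the severity down. The small open-label design and the formal 5% test are the reasons to correct it all the same.

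**What to change.** 1. In the abstract, in Methods (Primary clinical outcomes) and in Statistical analysis (Primary clinical outcomes), state one primary outcome in the same words: the between-group difference in change in shoulder pain VAS from visit 1 to visit 11. Naming the between-group comparison matters because the null and alternative hypotheses are now worded as applying within each group.
2. Account for baseline VAS in the primary model, for instance as a covariate with the post-baseline visits as the responses. Level and change then give the same treatment effect.
3. In the abstract and in Statistical analysis (Secondary clinical outcomes), correct the secondary VAS time point to visit 12, to match the Methods list.

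The cost is a few sentences of wording and one covariate that is already collected. No visits, participants or measurements are added, and 15 per group stands.

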#### VAS on shoulder pain

Subjects will explain their pain severity on a scale. The left end of the line is 0 (no pain), and the right end is 100 (worst possible pain). Physicians measure the length from the zero point to the patient’s mark and convert it to the VAS score. Participants will indicate their previous night’s shoulder pain on the line by marking a horizontal line, and the assessor will measure the position of the recorded line [17].

